## Abstract

Background: Parkinson’s disease (PD) patients who receive deep brain stimulation (DBS) have a higher risk of postoperative pain, which will affect their postoperative quality of recovery (QoR). Scalp nerve block (SNB) and intercostal nerve block (ICNB) can alleviate postoperative pain, yet their effect on postoperative QoR in PD patients has proven to be unclear. Therefore, we have aimed to explore the effect of SNB paired with ICNB on postoperative QoR. Methods: To explore the effect, we have designed a randomized controlled trial in which 88 patients with PD will be randomly assigned to either an SNB group or control group, receiving either SNB combined with ICNB or without before surgery. The primary outcome will be a 15-item QoR score at 24 h after surgery. The secondary outcomes will include: 15-item QoR scores at 72 h and 1 month after surgery; the numeric rating scale pain scores before discharge from the postanesthesia care unit (PACU) at 24 h, 72 h, and 1 month after surgery; rescue analgesics; nausea and vomiting 24 h after operation and remifentanil consumption during operation; emergence agitation; the duration of anesthesia and surgery; time to respiratory recovery, time to response, and time to extubation; the PACU length of stay; as well as adverse events. Proposed protocol and conclusion: Our findings will provide a novel method for the management of recovery and acute pain after DBS in PD patients. This research was registered at clinicaltrials.gov NCT05353764 on 19 April 2022.

## 1. Introduction

Parkinson’s disease (PD) is a prevalent neurodegenerative disease characterized mostly by motor symptoms such as tremor, rigidity, postural instability, bradykinesia, and postural reflex impairment [1,2]. Moreover, non-motor symptoms such as autonomic impairment and cognitive dysfunction may occur prior to the motor syndrome [3,4]. More than 6.1 million people experience multisystem symptoms of PD globally [5]. Although drug therapy can alleviate motor symptoms, there have been few effective treatment strategies for advanced PD [6]. Given the side effects of drug therapy, deep brain stimulation (DBS) is the most well established and reliable therapy for the motor fluctuations and symptoms in patients with advanced PD [7].

Most evidence has shown that DBS surgery can reduce PD-related pain [8,9,10]. However, PD patients undergoing DBS have a higher risk of perioperative complications, including postoperative pain which can worsen the recovery of patients, thus resulting in longer hospital stays and higher hospital costs [11,12]. A previous study has shown that analgesic methods were administrated less frequently for neurosurgery than other operations [13], and clinicians often fail to provide early sufficient postoperative analgesia due to the early assessment of consciousness. Recent studies have shown that up to 80% of patients suffered moderate-to-severe pain following neurosurgery [14,15,16]. So far, few studies have explored effective analgesic methods for DBS surgery.

Recently, opioid consumption in patients with moderate-to-severe postoperative pain has increased gradually, which has been followed by adverse events such as nausea, vomiting, respiratory depression, itchy skin, and drug dependency [17]. Therefore, multiple clinical studies have adopted nerve blocks instead of opioids to treat acute postoperative pain following craniotomy [18,19]. A previous study has shown that scalp nerve block (SNB) with ropivacaine can provide perioperative analgesia and reduce pain-related complications [20]. In addition, acute pain after thoracotomy has been found to be reduced by intercostal nerve block (ICNB) [21]. Therefore, ICNB may relieve postoperative pain in DBS surgery due to the site of the anterior chest incision. However, there is a shortage of evidence to show that SNB combined with ICNB reduces pain and improves the quality of recovery (QoR) after DBS surgery.

The SNB—the blockage of nerves including the greater occipital nerve, superficial temporal nerve, trochlear nerve, and supraorbital nerve—was developed because of its potential advantages for powerful regional anesthesia administration. Moreover, it encourages the advancement of precise neurosurgery, functional, and micro-neurosurgery [22]. The ICNB was used to provide effective postoperative analgesia in chest surgery [21,23]. The incision of DBS surgery involves the distribution of scalp nerves and intercostal nerves; thus, SNB combined with ICNB may relieve postoperative pain in patients receiving DBS surgery.

The 15-item QoR (QoR-15) questionnaire is an outcome questionnaire reported by patients that assesses the quality of recovery following surgery and anesthesia [24]. The QoR-15 score includes five areas of health status reported by patients in order to provide a meaningful assessment of their total recovery experience: pain, physical comfort, physical independence, psychological state, and emotional state. It is a useful instrument in clinical studies or trials due to the measurement errors and reliability, and a higher QoR-15 score indicates better postoperative recovery.

The present study’s main objective is to evaluate the clinical efficacy of SNB combined with ICNB for the QoR after DBS surgery. Furthermore, the present study may provide a novel method for enhanced recovery and early prevention and treatment of acute pain after DBS surgery. We hypothesize that SNB combined with ICNB can improve the postoperative QoR of patients with PD. This is based on the clinical evidence that the involved region of the scalp and intercostal nerves can be blocked by SNB combined with ICNB, providing an extensive block and better analgesia.

We have designed a single-center, prospective, randomized controlled trial including 88 PD patients scheduled for DBS surgery. The primary outcome will be a QoR-15 score at 24 h after surgery. The secondary outcomes will include: QoR-15 scores at 72 h and 1 month after operation; the numeric rating scale (NRS) pain scores before discharge from the postanesthesia care unit (PACU) at 24 h, 72 h, and 1 month following surgery; rescue analgesics; nausea and vomiting 24 h following surgery and remifentanil consumption during operation; emergence agitation; the duration of anesthesia and surgery; time to respiratory recovery, time to response, and time to extubation; PACU length of stay (LOS); as well as nerve-block-related adverse events (AEs).

## 2. Materials and Methods

The study protocol has been completed and is in accordance with the SPIRIT PRO extension reporting guidelines [25]. Figure 1 depicts the study’s patient flow diagram, and Table 1 depicts the study schedule.

### 2.1. Study Design and Setting

This is a single-center, prospective, randomized, controlled trial that is designed to investigate the efficacy of the combination of ICNB and SNB using ropivacaine for QoR after the performance of surgery on patients with PD. From April 2022 to March 2023, patients with PD who receive elective DBS surgery will be recruited in Shanghai Changhai Hospital, the Naval Medical University.

Protocol changes are not expected. The inclusion and exclusion criteria are fairly well established; however, when a trial adjustment is required, any modification in the methodology or criteria will be reported to the whole research group in a conference. The final manuscript for journal submission will include all revisions.

#### 2.1.1. Primary Outcome

The study’s primary outcome is the scores of QoR-15 at 24 h after surgery.

#### 2.1.2. Secondary Outcomes

The scores of QoR-15 at 72 h and 1 month after surgery.The NRS scores before discharge from PACU at 24 h, 72 h, and 1 month after surgery; rescue analgesics; nausea and vomiting 24 h after surgery; remifentanil consumption during operation; emergence agitation; PACU LOS; and SNB-related adverse events.The duration of anesthesia and surgery, time to respiratory recovery, time to response, and time to extubation.

#### 2.1.3. Outcome Measures

The QoR-15 questionnaire will be used to measure the patients’ quality of recovery at 24 h, 72 h, and 1 month after operation. A higher QoR-15 score (from 0 to 150) suggests greater recovery after surgery. The NRS score will be used to measure postoperative pain, and a higher score indicates more severe pain after surgery. The NRS scores will be recorded before discharge from PACU at 24 h, 72 h, and 1 month following surgery. Neuropathic pain will be assessed before surgery by a modified Douleur Neuropathique 4 (DN4) questionnaire on a scale of 0–10. A total DN4 score of more than or equal to 4 indicates neuropathic pain.

Emergence agitation is identified as improper behavior that presents itself as excitation, agitation, and concurrent orientation disorder during the anesthesia recovery phase. Respiratory recovery time refers to the interval between the end of anesthetic drugs and respiratory recovery. Response time is defined as the interval between the cessation of anesthetic drugs and response to a verbal command. Duration of time between the cessation of anesthetic drugs and extubation is referred to as the extubation time.

#### 2.1.4. Sample Size and Recruitment

The study’s primary outcome is the scores of QoR-15 at 24 h after surgery. Our preliminary study showed that the scores of QoR-15 at 24 h following DBS operation in PD patients without nerve block were equivalent to 110 (10.1). A previous study has shown that the QoR-15 score change of 8 points was deemed to be a clinically significant difference [26]. We calculated the required number of patients using PASS 11 software (NCSS, Kaysville, UT, USA) with an alpha error of 0.05 and power 95% (test for two proportions, two-sided *t*-test), and determined that 35 patients would need to be included in each group. Considering a 20% dropout rate, we defined a sample size of 88 participants.

Recruitment will be performed during a 12-month period. The study will end when the last patient enrolled undergoes an assessment of QoR 1 month after surgery. The protocol has been initiated as planned in April 2022 and will be completed in March 2023.

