#### 2.5.4. Statistical Analysis

Masked statistical analysts will conduct the analyses at the Clinical Research Center of Changhai Hospital. The full analysis set including all randomized patients and per protocol set, including patients with the primary outcome, will be performed. Safety and efficacy analyses will be conducted based on the intention-to-treat analysis population, which includes all randomized patients. Missing data will be handled using the mixed model for repeated measurements.

All statistical analysis will be performed by SPSS 23.0 statistical analysis software (IBM SPSS, Armonk, NY, USA). Continuous variables in normally distributed data represented as mean (SD) will be compared using the Student’s t-test, while continuous variables in non-normal distribution data reported as medians (quartiles) will be compared using Mann-Whitney *u* test. Categorical variables described as frequency and percentages will be compared using χ^2^ test or Fisher’s exact test. *p* < 0.05 will be regarded as statistically significant.

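### The stated 95% power does not follow from the plan's own inputs: 35 evaluable patients per group give about 90%, and the calculation also names a test that does not fit the outcome

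*Protocol article*

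**What the plan says.** All the ingredients are in section 2.1.4 (Sample Size and Recruitment) of the protocol article.

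- **Outcome:** "The study’s primary outcome is the scores of QoR-15 at 24 h after surgery". Section 2.1.3 describes it as a score: "A higher QoR-15 score (from 0 to 150) suggests greater recovery after surgery".
- **Control value:** the preliminary study found that "the scores of QoR-15 at 24 h following DBS operation in PD patients without nerve block were equivalent to 110 (10.1").
- **Difference:** "the QoR-15 score change of 8 points was deemed to be a clinically significant difference".
- **Error rates and test:** "with an alpha error of 0.05 and power 95% (test for two proportions, two-sided" *t*-test).
- **Result:** the authors "determined that 35 patients would need to be included in each group", then allow for 20% dropout and reach 88 participants. Section 2.4 allocates them 1:1.

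For the analysis, section 2.5.4 plans a Student's *t*-test for normally distributed continuous variables, a Mann-Whitney test otherwise, and significance at *p* < 0.05.

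**The concern.** The section gives every input needed to repeat the calculation, and the stated result does not follow from them. For a difference of about 0.8 SD, 35 per group is the familiar answer for 90% power with a two-sided test, not for 95%. The bracket also names two incompatible procedures, a comparison of proportions and a *t*-test, so a reader cannot tell which calculation was run.

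This is the only sample size justification for the primary outcome. If the 95% figure is repeated in the results paper, a null finding will appear to come from a trial with a 1 in 20 chance of missing an 8-point benefit, when the planned evaluable sample carries nearly a 1 in 10 chance.

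**Working it through.** **Inputs**

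| Quantity | Value | Source |
|---|---|---|
| Difference | 8 points | 2.1.4 |
| SD | 10.1 | 2.1.4; section 2.5.4 reports normal data as mean (SD), so the bracketed figure is read as an SD |
| Alpha | 0.05, two-sided | 2.1.4 |
| Stated power | 95% | 2.1.4 |
| Evaluable per group | 35 | 2.1.4 |
| Dropout | 20% | 2.1.4 |
| Allocation | 1:1 | 2.4 |

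Two assumptions are needed: the SD of 10.1, given only for patients without a block, applies to both groups, and the 8 points is the between-group difference entered. The standardised difference is then 8/10.1 = 0.792.

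**Step 1: try to reproduce 35 at 95% power.** The normal approximation for two means is n = 2(z₁₋α/₂ + z₁₋β)² SD²/difference².

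Two-sided 0.05, 95% power: 2 × (1.960 + 1.645)² × 10.1²/8² = 41.4, so 42 per group. The exact two-sample *t*-test (noncentral *t*) solves at 42.4, so 43 per group. Neither gives 35.

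**Step 2: find the power that 35 gives.** The noncentrality parameter is 8/(10.1 × √(2/35)) = 3.31 with 68 degrees of freedom and a two-sided critical value of 1.995. Power is 90.4% (91.2% by the normal approximation), so the type II error is 9.6%. The same calculation at other sizes:

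| Evaluable per group | Power, two-sided *t*-test |
|---|---|
| 35 | 90.4% |
| 40 | 93.8% |
| 42 | 94.8% |
| 43 | 95.3% |
| 44 | 95.7% |

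**Step 3: look for the origin of 35.**

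- Two-sided *t*-test at 90% power: n solves at 34.5, so 35. This is an exact match.
- One-sided 0.05 at 95% power: 2 × (1.645 + 1.645)² × 10.1²/8² = 34.5, so 35 by the normal approximation. The one-sided *t*-test gives 94.9% at 35 and needs 36. The text says two-sided.
- Two proportions, reading the means as 110/150 and 118/150: about 1,664 per group at 95% power. That test did not produce the number.
- At 35 per group, two-sided 95% power requires a difference of 8.83 or a common SD of 9.15. Neither value appears in the article.

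**Step 4: dropout.** 35/0.8 = 43.75, so 44 per group and 88 in total; the plan's inflation step is correct. For a true 95%, 43/0.8 = 53.75, so 54 per group and 108 in total.

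**The case against.** The strongest reply is that the section shows a mismatch without showing which entry is wrong. The 35 could come from a 90% power setting or from a one-sided alpha of 0.05, so the faulty item might be the sidedness rather than the power. Likewise 10.1 is given only for unblocked patients; with an SD of about 8.0 to 8.1 in the block group, 35 per group would reach 95%. The true origin cannot be settled from the article. But a one-sided test contradicts the stated two-sided one, and no smaller SD or larger difference is stated. However the 35 arose, a two-sided *t*-test on the stated inputs has about 90% power.

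The second reply concerns consequence. Ninety percent is adequate by usual standards, 44 per group will be randomised, and the 24 h score is collected on the ward, so losses may be below 20%. With no losses power is 95.7%. This is fair and limits the practical harm. It does not rescue the statement, which attaches 95% to 35 evaluable patients and treats the rest as a dropout allowance. It is also fair that a completed trial should be judged mainly by its estimate and confidence interval rather than its planned power.

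Third, the two-proportions wording is probably a reporting slip, because the fitting test stands in the same bracket and the planned analysis is suitable for a continuous score. That is accepted. It needs deleting, but it did not drive the number.

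**Conclusion.** The concern holds. On the plan's own two-sided inputs, 35 evaluable patients per group give 90.4% power, not 95%, and the type II error is 9.6% rather than 5%. Meeting the stated 95% would take 43 evaluable per group, 8 more than planned, and 20 more randomised patients overall (108 against 88). The gap is too large for rounding or for the choice between normal and *t* formulas (42 against 43).

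This rests on a common SD of 10.1 and a between-group difference of 8, the natural reading of the section. If the score were analysed by Mann-Whitney under normality, power at 35 per group would be about 89%. The error is in a stated design property and must be corrected, but the size of the trial is defensible at 90%.

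**What to change.** Keep 88 patients and restate the calculation, for example: *two-sample t-test, two-sided alpha 0.05, difference 8 points, common SD 10.1: 35 evaluable patients per group give 90% power; 44 randomised per group allow for 20% dropout.* Delete the reference to two proportions. The authors should check the saved PASS output when making the correction; if a different setting was used, such as a one-sided alpha, they should say so. The 95% figure should not be repeated in the results paper.

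The cost is one sentence in the protocol or an erratum and a slightly less favourable stated power. Recruitment and analysis are unchanged.

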### 2.2. Selection of Subjects

#### 2.2.1. Participants

Participants who will undergo elective DBS surgery will be informed of the trial before surgery. Interested participants can contact the research coordinator to acquire more information about the study purpose and protocol. The clinical research coordinator will interview potential subjects to assess whether they meet the inclusion and exclusion criteria. Written informed consent will be voluntarily provided by eligible participants to the research coordinator before randomization.

#### 2.2.2. Inclusion and Exclusion Criteria

Inclusion criteria:Aged ≥ 18;American Society of Anesthesiologists (ASA) physical status of I–III;Able to communicate normally.

Exclusion criteria:Allergy to local anesthetics;Pre-existing infection at block site;Severe coagulopathy;Pre-operative neuropathic pain state;DBS surgery history;Failing to give informed consent or lack of compliance.

### 2.3. Interventional Methods

#### 2.3.1. Intervention

Participants randomized to the SNB group will receive general anesthesia combined with SNB and ICNB using 0.5% ropivacaine, which will be performed exclusively by an attending anesthesiologist. Meanwhile, patients in the control group will receive general anesthesia without the nerve blocks. An attending anesthesiologist will select the sites of the nerve blocks based on the surgical incision site. After negative aspiration, the scalp nerve will be blocked, including the greater occipital nerve (2–3 mL), superficial temporal nerve (2–3 mL), trochlear nerve (2–3 mL), and supraorbital nerve (2–3 mL). The total volume in SNB will not exceed 10 mL.

Ultrasound-guided unilateral ICNB will be conducted at the plane of T4–T5 next to the sternum in patients who are in the supine position. A longitudinally oriented, linear ultrasonic probe will be used to determine the pleura, internal intercostal muscles, rib, and innermost intercostal muscles. An echogenic needle will be inserted using an in-plane technique to target the inferior margin of rib. A volume of 10–15 mL with 0.5% ropivacaine will be injected into the intercostal spaces where the incision locates after negative aspiration. ICNB is considered successful when pleural movement is observed in intercostal spaces.

The block efficacy for formal dermatomal sensory will not be formally tested because patients under general anesthesia are unconscious. The anesthesiologist performing the nerve blocks will not visit patients in the perioperative period. After the nerve blocks, the anesthesiologist will cover the dressing at the relevant areas to hide the allocation. Only the dressing will be covered in the same site of the control group without injecting normal saline, in consideration of ethical care.

#### 2.3.2. Criteria for Termination or Adjusting the Assigned Interventions

There will be no unique criteria for changing assigned interventions, but there are situations under which the research will be terminated: (1) postoperative surgical site bleeding; (2) serious DBS surgery-related complications (such as pulmonary aspiration, wound infection, respiratory insufficiency, and delirium) and nerve-block-related AEs (such as pneumothorax and local anesthetic toxicity); (3) unexpected postoperative continuation of intubation; and (4) unanticipated reoperation 24 h following surgery.

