### 2.5. Data Collection and Analysis

#### 2.5.1. Data Collection and Management

Researchers will explain the advantages of participating in the study to participants and their authorized surrogates before DBS surgery. A specific masked researcher will collect the patients’ basic characteristics before surgery. After the surgery, the blinded investigator will conduct a follow-up to record QoR-15 scores at 24 h and 72 h after surgery in the ward, and at 1 month after surgery in the outpatient clinic. Participants will be excluded if they are unable to complete the primary outcome measure. The anesthesiologists in charge will record the patients’ intraoperative data. Other data on secondary outcomes will be collected by a blinded investigator. The data collected will be first completed on a paper Case Report Form (CRF). Following this, the data manager will merge the double data into an electric database which will be examined by two inspectors.

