#### 2.5.2. Data Monitoring

The Data and Safety Monitoring Board (DSMB) of the Clinical Research Center in Changhai Hospital, which is made up of independent clinical specialists and statisticians with access to unblinded data, will monitor the study’s safety. Performance and safety of the study will be reviewed monthly by the DSMB, which is separate from the investigational site, the sponsor, and any conflicting interests. The criteria for terminating the study for a given trial participant have been described previously. The allocated intervention for participants will be revealed by the DSMB, which will also make the final decision to end the study.

The complete, anonymous final data set will be accessible to the data manager in Changhai Hospital’s Clinical Research Center. Others will have access to the final data set following the approval of the DSMB in the Clinical Research Center.

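### Ending the research for a participant after outcome-related events, some possible only in the block arm, conflicts with the promised analysis of all randomised patients and can bias it

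*Protocol article*

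**What the plan says.** - **Section 2.3.2** gives no particular criteria for changing the assigned intervention, and then says "there are situations under which the research will be terminated: (1) postoperative surgical site bleeding; (2) serious DBS surgery-related complications". The list continues with "nerve-block-related AEs (such as pneumothorax and local anesthetic toxicity); (3) unexpected postoperative continuation of intubation; and (4) unanticipated reoperation 24 h following surgery".
- **Section 2.5.2 (Data Monitoring)** fixes the level at which this applies: "The criteria for terminating the study for a given trial participant have been described previously". These are rules for one participant, not stopping rules for the whole trial.
- **Outcomes.** Block-related adverse events are a secondary outcome. The Introduction ends its list with "as well as nerve-block-related adverse events (AEs" and section 2.1.2 has "emergence agitation; PACU LOS; and SNB-related adverse events". Time to extubation and length of PACU stay are also secondary outcomes.
- **Section 2.5.1 (Data Collection and Management)** adds: "Participants will be excluded if they are unable to complete the primary outcome measure".
- **Section 2.5.4 (Statistical Analysis)** bases efficacy and safety on the intention-to-treat population of all randomised patients. It assigns missing data to a mixed model for repeated measurements and defines the per-protocol set as patients with the primary outcome.
- **Table 1** schedules QoR-15 at 24 h, 72 h and 1 month only, and adverse events from postinduction to 1 month.

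**The concern.** After randomisation, a patient's data should not stop because of how the patient fares. Here the triggers for ending participation are complications. Some are listed outcomes or bear directly on them, and block-caused ones cannot arise in controls, who receive only a dressing (section 2.3.1). If follow-up stops at these events, patients likely to have recovered badly lose their QoR-15 and pain scores and their later adverse-event visits. For block-caused events the control arm has no matching loss. The primary comparison could then favour the blocks for a reason unrelated to their benefit, and the safety record would be shorter for the patients who were harmed. Data not collected at 24 h cannot be recovered afterwards.

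**Working it through.** **1. What termination can mean.** Section 2.3.2 sets termination apart from changes to the intervention. Section 2.4 and Table 1 place the blocks after induction, once. By the time of postoperative bleeding, continued intubation, wound infection or reoperation, no study treatment remains to be stopped. What remains is follow-up.

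**2. Which triggers touch outcomes, and in which arm.**

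| Trigger | Relation to listed outcomes | Arm |
|---|---|---|
| "nerve-block-related AEs (such as pneumothorax and local anesthetic toxicity") | Secondary outcome | Block-caused events: SNB only |
| "unexpected postoperative continuation of intubation" | Bears on extubation time and PACU stay | Either |
| Bleeding, serious surgical complications, reoperation | Not listed as outcomes, but likely to lower QoR-15 | Either |

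**3. Whether the analysis plan repairs it.** A mixed model uses a patient's observed scores to inform the missing ones. With no baseline QoR-15, a patient stopped before 24 h supplies no score at all. Under missing at random that patient is in effect taken to recover like the rest of the arm, which is implausible when a complication caused the loss. The exclusion in section 2.5.1 leads to the same result.

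**4. Size.** The plan gives no event rate and no QoR-15 value for such patients, so it has no figure of its own to reproduce on this point. Inputs from section 2.1.4: target difference 8 points; 110 (10.1), reading 10.1 as the SD; 35 per group and 20% dropout. The dropout step reproduces: 70 / 0.8 = 87.5, rounded up to 88, or 44 per arm. (The 35 itself does not reproduce for two-sided 95% power, which needs 42 by the normal approximation or 43 by the t-test. Nothing here depends on it.)

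If *k* of 44 patients are removed from one arm and would have scored *D* points below the rest, that arm's mean is overstated by (*k* / 44) × *D*. With assumed *k* of 1 to 4, *D* of 20 to 40, and SNB-only losses:

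| *k* | *D* = 20 | *D* = 40 |
|---|---|---|
| 1 | 0.45 (6% of 8) | 0.91 (11%) |
| 2 | 0.91 (11%) | 1.82 (23%) |
| 4 | 1.82 (23%) | 3.64 (45%) |

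If there were no true effect, the two-sided rejection rate would rise from 5% to about 5.5%, 7%, 13% and 37% for shifts of 0.45, 0.91, 1.82 and 3.64 (noncentral t, SD 10.1, 42 per arm).

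For events common to both arms, the net shift is (*k* in SNB − *k* in control) / 44 × *D*:
- 3 against 3: 0.
- 4 against 2: +0.91 to +1.82.
- 2 against 4: −0.91 to −1.82, that is, against the blocks.

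**The case against.** The strongest reply is that section 2.3.2 never says that visits stop or that collected data are discarded. Its heading is about assigned interventions, section 2.5.4 commits to all randomised patients, and this is a condensed article whose full protocol may cover follow-up after termination. The sentence in section 2.5.1 could also be read as merely defining the per-protocol set. This stands in part: loss of follow-up is the most natural reading, not a stated rule. But the article does fix a termination rule, an exclusion and an all-randomised analysis, and it does not say how they fit together.

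Four stronger readings are tempting and are not supported:
- *That termination can only mean the end of data collection.* The intervention consists of several scalp injections plus an intercostal block, and section 2.3.4 stops the blocks if toxicity is suspected. For that trigger there can be something to discontinue. The argument in step 1 holds for postoperative events.
- *That the rule as a whole favours the blocks.* Most triggers can occur in either arm, and if the blocks reduce complications the loss could work against them.
- *That the harms themselves go unrecorded.* Section 2.3.4 records all adverse events, and the triggering event is observed by definition. Only its later course and subsequent events are at risk.
- *That every trigger is a trial outcome, or that every one threatens the primary result.* Only block-related events are listed as outcomes, with continued intubation bearing on two others. Events after 24 h reach only the 72 h and 1 month results.

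**Conclusion.** The concern holds in a limited form. Sections 2.3.2, 2.5.1, 2.5.2 and 2.5.4 are not reconciled, and on their most natural reading they permit loss of outcome data that depends on outcome and is partly specific to one arm. The planned mixed model cannot repair this at 24 h. Bias towards the blocks is to be expected only from block-specific events before 24 h. For shared events the direction is unknown.

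The size cannot be derived from the documents. The 0.5 to 3.6 point range rests on assumed counts, assumed deficits and no matching control losses, and it is small if such events are rare. This should be fixed: the affected comparison is the primary one and the remedy is cheap, but the documents do not show that the result would be materially wrong.

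**What to change.** Reconcile the four sections with wording to this effect:
- The events in section 2.3.2 do not end outcome collection. QoR-15, NRS, recovery times and adverse events are collected at every scheduled time unless the participant withdraws consent.
- All randomised patients are analysed in their allocated arm. The exclusion in section 2.5.1 no longer applies to the primary analysis and, if kept, serves only to define the per-protocol set.
- In a rank analysis of extubation time, patients still intubated count as the longest times.
- Some patients may be unable to answer QoR-15 because of the event, whatever the rule says. For them, add a sensitivity analysis that assigns a poor score or the worst rank, and report the number and reason by arm.

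Clinical handling of the events, and unblinding where needed, are unaffected. The cost is protocol wording, some late or incomplete forms for a few patients, and a little more analysis. No visits are added.
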